#### Recruitment

Local clinicians will assess the patients in their respective unit for eligibility and competence to consent to participate. If a patient fulfills the criteria, the clinician informs the patient about the study and, if he or she wishes to participate, obtains a written informed consent. The clinician will then ask for permission to contact the closest relative to inform and possibly include her or him. We would like to include patients and relatives in dyadic pairs, but if this proves difficult, we might include relatives and patients separately. The recruitment process will follow a written and uniform procedure in both arms, where every eligible patient is asked to participate, to counteract selection bias. The inclusion period will start 1 month before the implementation start date, and continue for 12 months. Since many patients are discharged from specialist health care services to follow-up in their local municipalities after 1–2 years, recruitment has to start after the randomisation of clusters. This is to ensure that participating patients are still in treatment when the intervention units are ready to begin implementation. The clinical units will receive financial compensation for each pair recruited, and to promote retention, patients and relatives will each receive a symbolic compensation (gift card) after completing the third questionnaire. When this manuscript was submitted, the trial was actively recruiting patients and relatives.

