**Methods:**

The trial is cluster randomised, where 14 outpatient clusters from community mental health centres undergo stratified randomisation with an allocation ratio of 1:1. The seven intervention clusters will receive implementation support for 18 months, whereas the control clusters will receive the same support after this implementation period. The intervention consists of: 1. A basic level of family involvement and support. 2. Family psychoeducation in single-family groups. 3. Training and guidance of health care personnel. 4. A family coordinator and 5. Other implementation measures. Fidelity to the intervention will be measured four times in the intervention arm and two times in the control arm, and the differences in fidelity changes between the arms constitute the primary outcomes. In each arm, we aim to include 161 patients with psychotic disorders and their closest relative to fill in questionnaires at inclusion, 6 months and 12 months, measuring psychosocial health and satisfaction with services. Clinicians will contribute clinical data about patients at inclusion and 12 months. Use of health and welfare services and work participation, for both patients and relatives, will be retrieved from national registries. We will also perform qualitative interviews with patients, relatives, health care personnel and leaders. Finally, we will conduct a cost-effectiveness analysis and a political economy analysis.

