### Interventions

The clinical units in the intervention arm will receive implementation support for 18 months to assist the implementation of selected recommendations in the national guidelines. The control units will receive training and guidance only after this period. Meanwhile, control sites will not be obligated to follow any specific practice. Since the IFIP intervention is a complex intervention, this section is structured after the Medical Research Council (MRC)‘s framework to give a clear overview [30]. The framework was used actively to guide the development- and feasibility-stages described below.

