#### Data collection and outcomes

Clinicians will fill in a questionnaire with the patient’s demographic, social, and clinical data at inclusion. They will also score the Global assessment of functioning scale (GAF), split versions for symptoms and functioning [53], along with the Health of the Nation Outcome Scale (HoNOS). The latter instrument contains 12 items on a 5-point Likert-scale, assessing clinical problems and social functioning with reasonable adequacy. HoNOS has been generally acceptable to clinicians who have used it, is sensitive to change or the lack of it, showed good reliability in independent trials and compared reasonably well with equivalent items in the Brief Psychiatric Rating Scales and Role Functioning Scales [54]. Both instruments will be repeated after 12 months or upon discharge. Before starting recruitment, clinicians attended a 1.5-h long course in scoring HoNOS and GAF, to improve the reliability of these measurements. In the majority of our clinical sites, GAF was in frequent use and HoNOS was familiar to some clinicians. We choose these instruments partly because of their brevity to reduce the burden on local clinicians.

At inclusion only, relatives will provide general demographic and social data about themselves, and patients will be screened for drug and alcohol abuse with the 11-item ‘drug use disorders identification test (DUDIT) and the 10-item ‘alcohol use disorder identification test’ (AUDIT), respectively. Both self-reported instruments have shown satisfactory psychometric properties in clinical and non-clinical samples [55, 56].

Patients and relatives will fill in their respective questionnaires at inclusion, 6, and 12 months, containing the self-reported variables and instruments in Table 1. The self-reported instruments assess the psychosocial health of patient and relative, their experience of the mental health services, including shared decision-making, and the emotional climate between patient and relative. The latter is a primary target for family psychoeducation, whereas the two first domains might be affected by various degrees of improved family involvement and support. At the same time points, exposure to family psychoeducation for patients and relatives, and exposure to involvement and support measures for relatives will be reported. Adherence with medication will be monitored with a single question to the patient, relative and clinician.

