**Relatives’ self-reported outcomes**			
Experienced support	**CWS v2** [48], Carer Well-being and Support questionnaire, short version part B	18	L-4
Experience of caregiving	**ECI** [61], The Experience of Care-giving inventory questionnaire	66	L-5
Caregiver quality of life	**CarerQoL** [62], The Care Related Quality of Life questionnaire	7	L-3
Experienced shared decision making	An instrument inspired by **CollaboRATE** [59]	3	L-10
Expressed emotion	**FQ** [63], The Family questionnaire	20	L-4

^a^
*L* Likert scale and number of steps for each item

Number of psychiatric hospital admissions and days spent in hospital for patients will be obtained from national registries, for the period of 18 months before and 18 months after inclusion. Use of public health resources and work participation will be recorded for both patients and relatives over the same period of time, with data from national registries.

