### Research ethics

The study will only include participants who are competent to make the decision to participate in research. We will obtain both oral and written consent and the participants can withdraw from the study at any time, without giving any reason and without experiencing any consequences for their treatment. Patients with psychotic disorders can be considered a particularly vulnerable group and we have made considerable efforts to make our research responsive to their needs, while also ensuring that they stand to benefit from the knowledge we may generate.

By using a cluster randomised design, the project needs to include more patients than would a study with individual randomisation, and it is therefore important that the choice of study design is justified. Consent to be exposed to our intervention is also sought at cluster level and not from patients and relatives within the cluster. Family involvement is a low-risk intervention and the local clinicians must assess whether it is contraindicated for certain patients and relatives. We also maintain that the treatment options in the intervention clusters will improve, and that we do not reduce the quality of the services offered in the control arm. After the implementation period, we will offer training and guidance to the control clusters as well.

In the political economy analysis we will interview political leaders and health administrators about issues which might be controversial. Therefore, confidentiality and possibilities for additional individual interviews will be underlined. The interviews will not gather information in terms of personal or political party nature, and the results will have to be published in a generalised way, without reference to their particular source.

All our procedures are in accordance with national and international standards for research ethics, including the Helsinki Declaration [71]. The study has been approved by the Norwegian regional committee for medical and health research ethics (REC) South East with registration number 2018/128. Important protocol modifications will be reported to REC, and the trial registry at clinicaltrials.gov will also be updated.

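### Patient and relative follow-up runs past month 18, after which control clusters may receive the support at any time; nothing ties that start to the end of follow-up

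*Protocol article*

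**What the plan says.** All references are to the protocol article.

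- **Inclusion** (Recruitment): "The inclusion period will start 1 month before the implementation start date, and continue for 12 months".
- **Support in the intervention arm** (Interventions): "The clinical units in the intervention arm will receive implementation support for 18 months".
- **Support in the control arm**: the abstract says "whereas the control clusters will receive the same support after this implementation period". The Interventions section says "The control units will receive training and guidance only after this period". Research ethics says "After the implementation period, we will offer training and guidance to the control clusters as well". None of the three gives a date or makes the start wait for participant follow-up to finish.
- **Self-reported outcomes** (Data collection and outcomes): "Patients and relatives will fill in their respective questionnaires at inclusion, 6, and 12 months". For the clinician-rated GAF and HoNOS: "Both instruments will be repeated after 12 months or upon discharge".
- **Registry outcomes** (text after Table 1): admissions and hospital days are collected "for the period of 18 months before and 18 months after inclusion". Service use and work participation follow the same window, for patients and relatives.

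The Data analysis section compares the arms by intention to treat. Its sensitivity analyses concern complete outcome data and persisting diagnosis, not time after the control start.

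**The concern.** Follow-up is counted from each participant's own inclusion, while the control roll-out is counted from the implementation start. With inclusion open until month 11, the two clocks can overlap. Control participants may then be observed while their unit receives the support, yet still be analysed as unsupported. If the support works, the arms move closer together.

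The outcomes exposed are the 12-month questionnaires, GAF and HoNOS at 12 months, admissions, hospital days, service use, work participation, and the costs in the economic evaluation. All are secondary. They still matter to the design: the sample size section for clusters says 4 clusters per arm were enough for fidelity, and 7 were recruited to power the patient and relative study.

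A related problem sits before inclusion. The registry look-back is anchored at inclusion, so for most participants in the intervention arm it already contains months of implementation. Used as a baseline, it would absorb part of any effect in that arm only.

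**Working it through.** The article gives no figure for this overlap, so there is none to reproduce. The inputs are its own dates.

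**Timeline (implementation start = month 0; t = month of inclusion)**

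- t runs from -1 to -1 + 12 = 11.
- 6-month questionnaire at t + 6: months 5 to 17, all before month 18.
- 12-month questionnaire at t + 12: months 11 to 23. It falls after month 18 if t > 6.
- Registry window closes at t + 18: months 17 to 29. It passes month 18 if t > 0.

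**Shares after the control start S.** Two assumptions are needed: uniform accrual over the 12 months, and a value for S, since the article says only that it comes after month 18.

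- 12-month questionnaires after S: max(0, 23 - S)/12.
- Registry windows touched: max(0, 29 - S)/12.
- Share of post-inclusion registry time after S: (29 - S)²/(2 × 12 × 18) = (29 - S)²/432, for S up to 29.

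| Control start S | 12-month questionnaires after S | Registry windows touched | Registry time after S |
|---|---|---|---|
| 18 (earliest) | 5/12 = 42% | 11/12 = 92% | 121/432 = 28% |
| 21 | 2/12 = 17% | 8/12 = 67% | 64/432 = 15% |
| 23 | 0% | 6/12 = 50% | 36/432 = 8% |
| 24 | 0% | 5/12 = 42% | 25/432 = 6% |
| 29 | 0% | 0% | 0% |

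At S = 18 the affected questionnaires are taken between 0 and 5 months into control support, 2.5 on average. Averaged over all participants, the overlap is 25/24 = 1.04 of 12 months, or 8.7% of 12-month follow-up time. If inclusion is read as lasting 12 months from the implementation start itself, the S = 18 row becomes 46% of questionnaires, 92% of windows and 31% of registry time.

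**Registry period before inclusion, intervention arm.** It covers t - 18 to t, so it holds max(t, 0) months of implementation. The mean is 11²/(2 × 12) = 5.04 months, or 28% of 18, with a maximum of 11 months. This does not depend on S.

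**What the shares mean for the effect.** They bound the attenuation and do not estimate it. The contrast would shrink by the full 42% or 28% only if support produced its whole effect in control participants at once. If early support has no effect, it shrinks by zero.

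**The case against.** The strongest reply has five parts.

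1. **Month 18 is only the earliest start.** A reader might infer that control clusters begin at month 18, with 42% and 28% as the expected overlap. The article does not say so, and a start at month 24 would leave every questionnaire clean. The design figure is not available here, and a fuller calendar may exist elsewhere. This stands, and is why the result is given as a range. It does not remove the point, because the article states the other dates and leaves the roll-out free to fall inside follow-up.
2. **Effects take time and do not reach everyone.** The Discussion says complex practices need time to implement. Participants need not receive any specific intervention, and many patients are discharged to their municipalities after 1-2 years while registry follow-up continues. This stands: the true attenuation is probably well below the upper bounds.
3. **Exposure at inclusion is disclosed.** The Discussion says participants are likely to have some exposure at inclusion, explains why recruitment follows randomisation, and hopes to track part of this by questionnaire. This also stands. It would be wrong to say the authors overlooked it. But the passage does not deal with the registry look-back, or with control time after roll-out.
4. **A null result is not uninterpretable.** A reader might infer that it would be. The primary outcome is measured at month 18, all 6-month questionnaires are clean, and 58% of 12-month questionnaires fall by month 18 even at the earliest start. A null registry or cost result would be ambiguous, no more.
5. **Cut-offs and covariates belong in an analysis plan.** Largely true, and their absence is not the complaint. The complaint is a set of design dates that conflict unless the control start is fixed. Making a truncated 12-month contrast the main analysis would also discard late recruits in the intervention arm, who joined when implementation was most mature, so that is not recommended.

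**Conclusion.** The point holds for secondary outcomes. By the article's own dates, 12-month questionnaires run to month 23 and registry windows to month 29, while control support may begin at any time after month 18. Under uniform accrual, the overlap ranges from 42% of control 12-month questionnaires and 28% of control registry time (start at month 18) to 0% and about 6% (start at month 24). Questionnaires are free of overlap only from a month-23 start, and registry follow-up only from month 29.

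If the support works, the bias is towards no difference. Its size lies between zero and those shares, and the documents do not allow it to be placed more exactly. Separately, the registry period before inclusion holds on average about 5 of 18 months of implementation in the intervention arm, whatever the control start date. The fidelity primary outcome and the 6-month questionnaires are not affected.

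**What to change.** 1. **Control start date.** State it, and reconcile it with the last 12-month questionnaire at month 23. If it is no earlier than that, the questionnaire problem disappears.
2. **Registry outcomes and costs.** Censor follow-up in both arms at the control start date, with person-time as offset. Report the full-window intention-to-treat result beside it.
3. **12-month questionnaires.** Keep the all-data intention-to-treat analysis. Add a prespecified sensitivity analysis limited, by inclusion date and in both arms, to measurements due before the control start. Selecting on inclusion date does not depend on outcome.
4. **Registry baseline.** Do not adjust for the inclusion-anchored look-back as if it were unexposed. Use the period ending at implementation start as the baseline covariate.

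**Cost.** Mostly wording in the analysis plan and the registry request. Censoring loses up to about 28% of registry person-time (month-18 start), or about 6% (month-24 start), and intervals in the restricted analyses are wider. Moving the baseline leaves up to 11 months before inclusion in neither window. To keep a full 18-month baseline, the extract must reach back up to 11 + 18 = 29 months before inclusion for the latest recruits. Otherwise they have 18 - 11 = 7 unexposed months.

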#### Data collection and outcomes

Clinicians will fill in a questionnaire with the patient’s demographic, social, and clinical data at inclusion. They will also score the Global assessment of functioning scale (GAF), split versions for symptoms and functioning [53], along with the Health of the Nation Outcome Scale (HoNOS). The latter instrument contains 12 items on a 5-point Likert-scale, assessing clinical problems and social functioning with reasonable adequacy. HoNOS has been generally acceptable to clinicians who have used it, is sensitive to change or the lack of it, showed good reliability in independent trials and compared reasonably well with equivalent items in the Brief Psychiatric Rating Scales and Role Functioning Scales [54]. Both instruments will be repeated after 12 months or upon discharge. Before starting recruitment, clinicians attended a 1.5-h long course in scoring HoNOS and GAF, to improve the reliability of these measurements. In the majority of our clinical sites, GAF was in frequent use and HoNOS was familiar to some clinicians. We choose these instruments partly because of their brevity to reduce the burden on local clinicians.

At inclusion only, relatives will provide general demographic and social data about themselves, and patients will be screened for drug and alcohol abuse with the 11-item ‘drug use disorders identification test (DUDIT) and the 10-item ‘alcohol use disorder identification test’ (AUDIT), respectively. Both self-reported instruments have shown satisfactory psychometric properties in clinical and non-clinical samples [55, 56].

Patients and relatives will fill in their respective questionnaires at inclusion, 6, and 12 months, containing the self-reported variables and instruments in Table 1. The self-reported instruments assess the psychosocial health of patient and relative, their experience of the mental health services, including shared decision-making, and the emotional climate between patient and relative. The latter is a primary target for family psychoeducation, whereas the two first domains might be affected by various degrees of improved family involvement and support. At the same time points, exposure to family psychoeducation for patients and relatives, and exposure to involvement and support measures for relatives will be reported. Adherence with medication will be monitored with a single question to the patient, relative and clinician.

**Table 1 Tab1:** Self-reported variables and instruments at inclusion, 6 and 12 months

Variable	Instrument	Items	Scale^a^
**Patients’ self-reported outcomes**			
Experience of mental health and functioning	**Basis-24** [47], The Behavior and Symptom Identification scale	24	L-5
Quality of life	**ReQoL-10** [57], The Recovering Quality of Life questionnaire	10	L-5
Perceived criticism and warmth from relative	**PCW** [58], Perceived criticism and warmth	5	L-10
Experienced shared decision making	**CollaboRATE** [59]	3	L-10
General satisfaction	**MANSA** [60], the Manchester Short Assessment of Quality of Life – first item	1	L-7
Experienced burden of mental health problems	IFIP trial question	1	L-7
**Relatives’ self-reported outcomes**			
Experienced support	**CWS v2** [48], Carer Well-being and Support questionnaire, short version part B	18	L-4
Experience of caregiving	**ECI** [61], The Experience of Care-giving inventory questionnaire	66	L-5
Caregiver quality of life	**CarerQoL** [62], The Care Related Quality of Life questionnaire	7	L-3
Experienced shared decision making	An instrument inspired by **CollaboRATE** [59]	3	L-10
Expressed emotion	**FQ** [63], The Family questionnaire	20	L-4

^a^
*L* Likert scale and number of steps for each item

Number of psychiatric hospital admissions and days spent in hospital for patients will be obtained from national registries, for the period of 18 months before and 18 months after inclusion. Use of public health resources and work participation will be recorded for both patients and relatives over the same period of time, with data from national registries.

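### Registry follow-up of 18 months from each inclusion runs past the point at which control clusters become due for the same support, so the arms converge late in the window

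*Protocol article*

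**What the plan says.** Four statements in the protocol article set the clocks.

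- **Registry window.** The text after Table 1 (Data collection and outcomes) takes psychiatric admissions and hospital days from national registries "for the period of 18 months before and 18 months after inclusion". It adds: "Use of public health resources and work participation will be recorded for both patients and relatives over the same period of time".
- **Accrual.** Recruitment: "The inclusion period will start 1 month before the implementation start date, and continue for 12 months".
- **Support in the intervention arm.** Interventions: "The clinical units in the intervention arm will receive implementation support for 18 months".
- **Support in the control arm.** The abstract says "the control clusters will receive the same support after this implementation period". Interventions says "The control units will receive training and guidance only after this period", and Research ethics says "After the implementation period, we will offer training and guidance to the control clusters as well". None of the three gives a start date.

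The Data analysis section compares the arms by intention to treat with mixed models and mentions no cut at the end of the implementation period. The Discussion covers exposure at inclusion and the new clinical pathways, but not this overlap.

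**The concern.** The registry window is tied to each person's inclusion, whereas the randomised difference in support is tied to the calendar of the implementation period. Anyone included after implementation start is followed past month 18, and from then on the control clusters may be receiving what the intervention clusters had. If support works in the same direction in both arms, that last stretch pulls the registry contrast towards no difference.

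Two uses of the data are at stake. The Blinding section relies on registry data as less open to experimenter bias in a trial that cannot be blinded, so a diluted registry contrast weakens one of its safeguards. The Health economics section also counts health care use and production loss as costs. If those figures come from this window, the usual-implementation comparator would include care given during the control roll-out.

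**Working it through.** The article gives no overlap figure to reproduce, so the check builds one from its stated timings.

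**Inputs.** Time is in months from implementation start. Inclusion time t runs from -1 to 11 (Recruitment, 12 months in total). The window ends at t + 18. Intervention support runs from 0 to 18. Two assumptions are added: t is uniform, and control support starts at month 18.

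**Overlap**

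- Window end: -1 + 18 = 17 to 11 + 18 = 29.
- Share of windows passing month 18: P(t > 0) = 11/12 = 91.7%, about 148 of the 161 controls to be recruited.
- Mean overlap: E[max(t, 0)] = (11²/2)/12 = 60.5/12 = 5.04 months. As a share of follow-up, 5.04/18 = 28%. The maximum is 11 months.
- If the 12 months are counted from implementation start instead (t from -1 to 12): 12/13 = 92.3%, mean 5.5 months (31%), maximum 12.
- If accrual is linearly front-loaded or back-loaded on -1 to 11: 84% or 99% have some overlap.

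**Loss of contrast.** Suppose the effect of support rises linearly over B months and then stays, in both arms. The effect accumulated by x months of support is G(x) = x²/(2B) for 0 < x < B, and x - B/2 after that (G(x) = x when B = 0, and zero for x ≤ 0). Over one window the intervention arm collects G(t + 18) - G(t), and the control arm collects G(t). The proportional loss is E[G(t)] / E[G(t + 18) - G(t)].

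| Build-up B (months) | E[G(t)], control | E[G(t + 18) - G(t)], intervention | Loss |
|---|---|---|---|
| 0 | 60.5/12 = 5.04 | 23 - 5.04 = 17.96 | 28% |
| 6 | (6 + 27.5)/12 = 2.79 | 20 - 2.79 = 17.21 | 16% |
| 12 | (1331/72)/12 = 1.54 | 17 - 1.54 = 15.46 | 10% |
| 18 | (1331/108)/12 = 1.03 | 14.00 - 1.03 = 12.97 | 8% |

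**Control start date.** With an immediate effect, a start 3 months after month 18 gives 2.67/17.96 = 15%, and 6 months gives 1.04/17.96 = 6%. The share with any overlap falls to 67% and 42%.

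**Effect of censoring at month 18.** Follow-up becomes min(18, 18 - t), with mean 18 - 5.04 = 12.96 months and minimum 7. The table gives the mean contrast per person-month and, as a rough signal measure, that contrast times the square root of mean follow-up.

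| B | Contrast, full window | Contrast, censored | Signal, full window | Signal, censored |
|---|---|---|---|---|
| 0 | 0.72 | 1.00 | 3.04 | 3.59 |
| 6 | 0.80 | 0.94 | 3.40 | 3.38 |
| 12 | 0.77 | 0.80 | 3.28 | 2.89 |
| 18 | 0.66 | 0.61 | 2.82 | 2.20 |

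Censoring removes the roll-out time. On this measure it gains clearly only when support works at once, and it loses when the effect takes 12 to 18 months to build.

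**The case against.** The strongest reply has four parts.

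1. **Retrieval is not analysis.** The 18 months may describe what is requested from the registries, and a censoring rule could stand in an analysis plan not shown here. This is fair as far as it goes. But the article itself fixes both the window and the control roll-out, and read together they mix roll-out time into the comparison unless something further is said.
2. **The size rests on a date the article does not give.** Support comes after the period, and Research ethics only says that it will be offered. A late start or partial uptake shrinks the problem. Recruitment also notes that many patients are discharged after one to two years, so some controls will have left before their unit is supported. All of this stands and lowers the figures.
3. **Effects probably build slowly.** The Discussion says that complex practices take time to implement, which makes the 10% and 8% rows at least as plausible as 28%. This stands.
4. **A mandatory cut can cost more than it saves.** It drops intervention-arm time when practice is most mature and leaves late recruits with as little as 7 months. The second table supports this.

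The cost-effectiveness link is also an inference: Health economics states no time horizon for costs.

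**Conclusion.** The overlap is real and follows from the article's own timings. Under uniform accrual and control support from exactly month 18, about 92% of participants have some overlap and about 28% of follow-up time is affected. The loss of contrast is 28% for an immediate effect and 16%, 10% or 8% for a build-up over 6, 12 or 18 months. It is smaller if control support starts later or controls are discharged first. The probable direction is towards no difference.

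A reader might infer that the arms swap roles after month 18. The documents do not support that: the implementation strategy section says that units are encouraged to keep training, guidance and the family coordinator permanently, so the arms converge. The loss figures above already assume that the intervention effect persists. A true swap would give about 56% for an immediate effect ((2 × 5.04)/17.96). A reader might also take 92% as the share of control follow-up affected, but it counts anyone whose window passes month 18 at all, even by a day.

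The consequence is limited. The sample-size section classes all patient and relative outcomes as secondary. The primary outcome, change in fidelity at 18 months, is unaffected.

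**What to change.** 1. Record the date on which support begins in each control cluster.
2. Keep the full 18-month comparison. Beside it, prespecify a between-arm analysis of the registry outcomes censored in both arms at one common calendar date, the start of control support, with person-time as an offset.
3. Apply the same cut as a sensitivity analysis to any cost inputs drawn from this window.
4. State with the full-window result that it includes control roll-out time and is probably biased towards no difference.

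Provided the registry records are dated, this needs analysis wording and a log of dates, with no new data collection. The price is precision: mean follow-up in the censored analysis falls from 18 to about 13 months, and late intervention-arm time is lost. For that reason it should be reported beside the full-window analysis and not replace it.
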